## **Protocol Summary**

### **Research aim**

This study is a phase II randomised controlled trial (RCT) of ParentChat, an adapted online parenting support group programme for parents and caregivers with children aged 2 to 17 in Udon Thani, Thailand. ParentChat provides evidence-based parenting information and interactive learning experiences via group-based online discussions using text, audio, and visual messages. This study aims to evaluate the preliminary effectiveness of ParentChat as an intervention to reduce child maltreatment (physical abuse and emotional abuse) and improve positive parenting, parenting stress, attitudes to corporal punishment, child behaviour problems, parental mental health, parent exposure to intimate partner violence (IPV), child/adolescent exposure to risks, online safety, child learning and development, and parent support of education.

This phase II RCT will also evaluate the feasibility and acceptability of the locally adapted version by assessing the operational process, which will include implementation fidelity, programme adherence, participant satisfaction, acceptability, and feasibility.

### **Objectives**

The objectives of the RCT are:

1. To evaluate the initial effects of the adapted ParentChat at one-month post-intervention and at the fourth and eighth weeks during programme delivery on the primary outcome of child maltreatment (physical and emotional abuse) and the proximal outcomes of positive parenting and parenting stress.
2. To evaluate at one-month post-intervention the initial effects of ParentChat on the secondary outcomes of attitudes to corporal punishment, child behaviour problems, parental mental health, and parent exposure to intimate partner violence, child/adolescent exposure to risks, online safety, child learning and development, and parent support of education.
3. To test the feasibility of the Thai ParentChat system by assessing:
  - a. Implementation fidelity
  - b. Programme adherence
  - c. Participant satisfaction
  - d. Acceptability and feasibility

### **Participants**

Participants will include 240 parents or primary caregivers (n=120 in the intervention group, n=120 in the control group) with a child between the ages of 2 and 17 from Udon Thani, Thailand. We will also conduct a focus group with all 6 facilitators who deliver the programme and will interview 12 programme participants to assess programme acceptability and feasibility.

## **Data collection and analysis**

Quantitative outcome data will be collected electronically at baseline and one-month post-intervention by data collectors at participants' homes. Abbreviated versions of standard, validated scales to assess the effect of the programme on the primary outcomes will be included in the survey. Computer-Assisted Self-Interviewing ('CASI') software will be used for sensitive items. If an appointment for an in-person meeting with the data collectors cannot be scheduled, participants will be interviewed telephonically. During programme delivery, programme participants will also be asked to complete a brief survey over the phone at weeks four, and eight, which will focus on primary and proximal outcomes. Data will be analysed using Stata 17. Multilevel linear regression or Poisson/negative binomial regression will be used to evaluate the intervention effects on the primary and secondary outcomes of interest.

Qualitative data will be collected via a focus group with facilitators and individual interviews with programme participants to evaluate the feasibility and acceptability of the online support group programme.

## **B. Background**

### **B.1. Literature review**

One billion children between the ages of 2 and 17, or 1 in 2 children worldwide, are estimated to experience violence each year . The situation is no different in Thailand, where a recent survey found that 53.8% of children aged 1 to 14 had experienced violent discipline . Violence against children (VAC) is a significant problem that has both short and long-term consequences on health, society, and the economy . Adverse outcomes include poorer cognitive abilities in early childhood, increases in externalising behaviour, increases in internalising behaviour, increases in aggressive behaviour, increased behaviour problems, inattention, and attention-deficit hyperactivity disorder (ADHD), depression, smoking, heavy alcohol use, problematic drug use, sexual risk taking, and mental ill health.

Evidence-based parenting programmes that support parents in their capacity to raise children in a positive, non-violent way have been effective at reducing VAC and improving a range of child and caregiver outcomes . An example is the Parenting for Lifelong Health (PLH) suite, a series of free, non-commercial parenting programmes developed with the aim to reduce violence in communities with limited resources. These programmes were developed and rigorously evaluated through a collaboration between the Universities of Oxford, Bangor and Reading in the United Kingdom, Stellenbosch University and the University of Cape Town in South Africa, WHO, and UNICEF. The programmes were originally developed and tested in South Africa and then adapted for other contexts, including Thailand . Evidence indicates that PLH parenting programmes reduce the risk of child maltreatment  and increase positive parenting . Additionally, PLH for Teens is cost-effective in reducing the abuse of adolescents in South Africa with an estimated lifetime saving of US\$2724 minimum per case . In Thailand, a feasibility pilot study of an adapted PLH for Young Children (PLH-YC) programme embedded within the Thai public health system showed that the programme reduced abusive and harsh parenting .

During the COVID-19 pandemic, there were several obstacles to implementing the in-person PLH programmes. During nationwide lockdowns and health emergencies, social contact is restricted. In addition, scaling prevention programming and public health interventions is commonly limited by the sustainability of

funding resources over time for service delivery , particularly for in-person programmes. Consequently, the programmes have been adapted using communication technology into an online parenting support group delivered via online text messaging platforms and the contents have been adapted for young children and adolescents. This adapted programme has been called ParentChat.

This study will evaluate ParentChat when delivered to caregivers in Thailand. We will use a hybrid approach with digital technology to reach out to the parents and caregivers to promote parent-led group learning, information gathering, and capacity development to support positive parenting and improve health and well-being. The primary focus is to provide families with information on parenting that is supported by research and to encourage interactive parenting education to meet the needs of parents.

## **B.2. Research aims**

This study aims to evaluate the preliminary effectiveness of ParentChat as an intervention for parents or caregivers with children aged 2 to 17 to reduce child maltreatment (physical abuse and emotional abuse) and improve positive parenting, parenting stress, attitudes to corporal punishment, child behaviour problems, parental mental health, parent exposure to IPV, child/adolescent exposure to risks, online safety, child learning and development, and parent support of education. This study will also assess the feasibility and acceptability of the locally adapted version by assessing the operational process, which will include implementation fidelity, programme adherence, participant satisfaction, acceptability, and feasibility.

## **B.3. Objectives**

The objectives of this study are:

1. To evaluate the initial effects of ParentChat on the primary outcome of physical and emotional abuse, and the proximal outcomes of positive parenting and parenting stress at one-month post-intervention and at the fourth and eighth weeks during programme delivery.
2. To evaluate the initial effects of ParentChat on the secondary outcomes of attitudes to corporal punishment, child behaviour problems, parental mental health, parent exposure to intimate partner violence, child/Adolescent exposure to risks, online safety, child learning and development, and parent support of education at one-month post-intervention.
3. To test the feasibility of the Thai ParentChat system by assessing:
  - a. Implementation fidelity
  - b. Programme adherence
  - c. Participant satisfaction
  - d. Acceptability and feasibility

## **B.4. Hypotheses**

1. Hypothesis 1: ParentChat will significantly reduce rates of child physical and emotional abuse, as measured by the ICAST-TP, in comparison to a control group.

2. Hypothesis 2: ParentChat will have a significant effect on the proximal outcomes including positive parenting and parenting stress, in comparison to a control group.
3. Hypothesis 3: ParentChat will have a significant effect on the secondary outcomes including improving positive parent involvement, attitudes to corporal punishment, child behaviour problems, parental mental health, parent exposure to IPV, child/adolescent exposure to risks, online safety, child learning and development, and parent support of education, in comparison to a control group.

### **C. Evaluation**

The preliminary efficacy and feasibility of ParentChat will be evaluated using both quantitative and qualitative methods. Data collection will be conducted at baseline, the fourth and eighth weeks during implementation, and one month post-intervention.

The evaluation will include the following activities:

- a) implementation of parenting intervention modules by local facilitators in hybrid delivery parent support groups (both in person and online);
- b) pre-post and the fourth, and eighth weeks assessments during programme delivery of the impact of the intervention on reducing child maltreatment, improving positive parenting, parenting stress, and addressing risk factors associated with VAC (attitudes to corporal punishment, child behaviour problems, parental mental health parent exposure to IPV, child/adolescent exposure to risks, online safety, child learning and development, and parent support of education.
- c) evaluating of implementation feasibility, programme adherence, participant satisfaction, and acceptability and feasibility.

#### **C.1 Study design**

This is a phase II RCT, observer-blinded, with two parallel groups, and designed to evaluate the preliminary effectiveness of ParentChat in reducing child physical and emotional abuse at immediate post-intervention. The study also aims to assess the feasibility and acceptability of the locally adapted version. Randomisation will be performed at the cluster level with a 1:1 allocation ratio.

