### *Programme delivery*

The 120 parents/primary caregivers in the intervention group will be divided into six groups of 20 participants who live in the same sub-districts. Each group will be overseen by one facilitator who will deliver the programme over nine weekly sessions. The group of six facilitators will receive weekly supervision from a trained coach during programme delivery.

Content for the adapted ParentChat programme include six core contents as following: 1) spending quality time with children; 2) talking with children to understand their feelings; 3) using praise and rewards to encourage positive behaviour; 4) establishing limits through effective instruction giving and consistent household rules; 5) nonviolent discipline strategies; and 6) problem solving with children.

Core activities during sessions will be delivered through LINE, a freeware application for instant communication. The programme will provide parents with activity assignments to complete with their children, including text/audio messages, illustrated comics, and videos. The facilitators will moderate text-based discussions around the parenting theme, support parents on an individual basis, and encourage them to apply the parenting skills at home. Parents will be prompted to give feedback regarding successes and challenges applying these parenting skills via audio or text messages during the week. When the next session begins, the facilitators will give a brief voice summary of the feedback and address possible solutions to a few key challenges. During implementation, participants will be supported with the necessary technical support, including IT support. Data bundles will be provided for internet access and to incentivise engagement.

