## **C.2 Outcome data collection**

Data collectors with experience working at the community level with low-income families will be recruited and trained extensively by the study team on ethics, informed consent, and data collection procedures. A detailed protocol will guide data collection to ensure consistency across data collectors. Surveys will be translated into Thai by the researchers and back-translated by an independent translator to ensure accuracy.

Data collection during the trial will take place at four time points. In addition to baseline and one-month post-intervention assessment, which will be done in person, assessments during programme delivery will be conducted telephonically during weeks four, and eight. These assessments will assess changes in target outcomes over the past two weeks.

During pre-post assessments, data collectors will visit participants' homes to complete surveys with them on tablets. Data collectors will sit beside participants and go through the survey together. To reduce the potential for error, data collectors will enter participants' responses into the tablet while showing them the screen. For sensitive sections of the questionnaire (i.e., those relating to IPV and physical/emotional abuse), the tablet is given to the parent, who is able to complete it on their own, using earphones to listen to the questions by audio if they have difficulties with literacy. If parents would prefer to continue completing the survey with the data collector for the sensitive items (as opposed to using CASI), they will continue to use this approach.

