### Primary outcome

#### *1. Child maltreatment – physical abuse and emotional abuse*

Four items adapted from a reduced version of the International Society for the Prevention of Child Abuse and Neglect (ISPCAN) Child Abuse Screening Tool-Trial Parent version (ICAST-TP)  will be used to determine physical abuse and emotional abuse. The evaluation will be repeated four times consisting of the evaluation at baseline, post-test, and every four weeks during programme delivery. This study will evaluate the incidence of child abuse both in overall abuse by combining all subscales of two items assessing physical abuse and two items assessing emotional abuse. Participants report on the incidence of violent discipline use over the past four weeks using a frequency score of 0 to 8 or more times (e.g., how often did you discipline by spanking, slapping, or hitting with their hand over the past 4 weeks.).

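### The design section places the primary effect immediately after the programme, when no assessment is scheduled, and the protocol names no single primary time or primary model for child maltreatment

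*Protocol*

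**What the plan says.** **Time of the effect.** Section C.1 (Study design) says the trial is "designed to evaluate the preliminary effectiveness of ParentChat in reducing child physical and emotional abuse at immediate post-intervention". Objective 1 in the Protocol Summary instead evaluates effects "at one-month post-intervention and at the fourth and eighth weeks during programme delivery on the primary outcome of child maltreatment", and section B.3 repeats this with "at one-month post-intervention and at the fourth and eighth weeks during programme delivery". Neither version says which of the three times leads. Hypothesis 1 in B.4 reads "ParentChat will significantly reduce rates of child physical and emotional abuse, as measured by the ICAST-TP, in comparison to a control group", with no time attached.

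**Assessments actually scheduled.** The opening of section C states: "Data collection will be conducted at baseline, the fourth and eighth weeks during implementation, and one month post-intervention". Section C.2 agrees: "In addition to baseline and one-month post-intervention assessment, which will be done in person", with telephone assessments in weeks four and eight. Facilitators "deliver the programme over nine weekly sessions" (C.1, Programme delivery).

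**Outcome.** The primary outcome in C.3 is an overall abuse score "combining all subscales of two items assessing physical abuse and two items assessing emotional abuse", reported over the past four weeks and measured four times.

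**Analysis.** Section C.4 sets two-tailed tests at 0.05. It plans a two-level model of post-intervention effects, adjusted for baseline, for all outcomes. It then adds a three-level model of time trends for child maltreatment and the proximal outcomes. Neither is called primary.

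**Sample size.** Section C.1 sizes the trial for one comparison of maltreatment frequency at 0.05 with power 0.8, and gives no assessment time.

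**The concern.** The design statement describes an effect that the trial cannot measure. The difference is one of substance because the abuse items look back four weeks. Asked right after session nine, they would cover the last weeks of delivery, while parents still have the facilitator and the group. Asked one month later, they cover the period after support has ended. The first is an effect under support and the second is persistence.

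The objectives do not settle which time is meant. The three listed times are not interchangeable. Week 4 comes after at most four of nine sessions. Weeks 4 and 8 are telephone interviews, whereas the post-test is planned in person with self-completion of the sensitive items. With two models covering the primary outcome and neither designated, the claim that abuse was reduced has no fixed basis before the data are seen, and the 0.05 used for the sample size does not belong to an identified test.

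**Working it through.** **1. Is there an immediate assessment?** The schedule is baseline, week 4, week 8 and one month after the programme. With nine weekly sessions, week 8 is still within delivery. No visit lies between the last session and one month, so the wording in C.1 matches no scheduled assessment.

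**2. What does the sample size spend?** Inputs from C.1 (Sample size): rate ratio 0.57, alpha 0.05, power 0.80, allocation 1:1, attrition 10%, design effect 2. Assumptions for the check: exponential test on the hazard difference, no censoring, two-sided, control hazard h1 = 1 (scale only), h2 = 0.57, mean hazard 0.785.

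N = [z(0.975)·√(4·0.785²) + z(0.80)·√(2·1² + 2·0.57²)]² / (1 − 0.57)²

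= [1.960·1.570 + 0.8416·1.628]² / 0.1849 = 106.96, which is 108 at equal allocation.

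108 / 0.90 = 120, and 120 × 2 = 240. All three stated figures reproduce. The whole two-sided 0.05 is spent on one comparison.

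**3. How many analyses of the primary outcome are planned?** C.4 plans two: the two-level post-intervention model and the three-level time-trend model. If significance in either could support the claim, the chance of at least one false positive under no effect is:

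- independent tests: 1 − 0.95² = 0.0975
- correlated tests (simulation, 1,000,000 draws of equicorrelated normal statistics): 0.091 at correlation 0.5, 0.084 at 0.7, 0.070 at 0.9

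The documents give no correlation, so these values are assumptions. Both models use the same post-test data, so a positive correlation is likely.

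**4. Upper illustration.** If Objective 1 were read as three separate tests, any of which could count:

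- independent tests: 1 − 0.95³ = 0.143
- correlated tests: 0.125 at correlation 0.5, 0.109 at 0.7, 0.084 at 0.9

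**5. Cost of keeping several co-equal tests with a Bonferroni split** (same formula as step 2):

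| Tests | Alpha each | Base N | After attrition | After design effect | Power at base N 108 |
|---|---|---|---|---|---|
| 1 | 0.05 | 108 | 120 | 240 | 0.80 |
| 2 | 0.025 | 130 | 145 | 290 | 0.72 |
| 3 | 0.0167 | 144 | 160 | 320 | 0.67 |

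Only a single designated test is consistent with the planned 240.

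**The case against.** The best defence is that the reference to an immediate effect is one isolated phrase. Both statements of Objective 1, the data collection summary, section C and section C.2 all give one month. Since no immediate visit exists, nobody could collect or analyse such data, and the practical harm from that phrase is small. This stands in part: the repair is one phrase. But the phrase sits in the sentence that defines the design, and neither Objective 1 nor Hypothesis 1 supplies a ranking to override it.

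A second defence is that the protocol leans towards the post-test. The summary calls the week 4 and 8 surveys brief, C.4 puts the post-intervention comparison first and introduces the trend model as an addition, and the sample size is for one comparison. That is a fair reading of the likely intention, but the protocol never states it.

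A third is that multiplicity rules and the ranking of models are commonly left to a statistical analysis plan, which is not at hand, and that this is a phase II study of preliminary effects. The absence of a multiplicity procedure is therefore not held against the protocol. What remains is the contradiction and the unranked objective in the protocol's own text, which a later plan would inherit.

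A reader might infer from Objective 1 that child maltreatment is tested at three times at 0.05 each, giving a 14% error. The protocol does not say so. Objective 1 speaks of evaluating effects, and C.4 specifies no separate contrast at week 4 or week 8; those times enter the trend model.

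**Conclusion.** The point holds. The design section and the assessment schedule contradict each other on when the primary effect is measured, and the protocol designates neither one time nor one model as primary for child maltreatment.

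The consequence is moderate. With the two planned models, the false-positive chance is 9.75% if the tests are independent and about 7% to 9% at assumed correlations of 0.9 to 0.5, against the 5% behind the sample size. This rests on the assumption that either model could support the claim, which the protocol neither states nor excludes. The 14% figure is only an upper illustration for three separate, independent tests and should not be quoted as the trial's error rate. The sample size arithmetic itself reproduces, and nothing here calls for more participants. The protocol should be corrected before the analysis begins.

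**What to change.** 1. In C.1 (Study design), replace the immediate time with one month post-intervention.
2. In Objective 1 (Protocol Summary and B.3) and Hypothesis 1 (B.4), name the combined four-item abuse score at the one-month assessment as the single primary endpoint. List the week 4 and week 8 effects on abuse as secondary.
3. In C.4, name the two-level baseline-adjusted post-intervention model as the one primary test of child maltreatment at two-sided 0.05, and label the three-level time-trend model secondary. Without this step the time would be fixed but two candidate tests would remain.

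The cost is wording only. Sample size, visits and data stay as they are, and the analysis then matches the single 0.05 comparison behind the 240. The one small loss is that an early effect at week 4 or week 8 can no longer carry the primary claim.

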##### *Eligibility criteria*

The following are the inclusion and exclusion criteria for participating parents or caregivers ( $n = 20$  per cluster):

Inclusion criteria for parents or caregivers:

1. Primary caregiver over the age of 18 years currently caring for child between the ages of 2 to 17;
2. Has regular contact with the child and lives with the child for at least 4 nights per week;
3. Has access to a smartphone and is willing and available to join an online parenting support group to share, learn and discuss parenting; and
4. Has provided consent to participate in the study.

Exclusion criteria for parents or caregivers

1. Exhibiting severe mental health problems or acute mental disabilities
2. Already participated in the PLH-YC Thailand programme or other parenting programmes. Other parenting programmes would not include Parent Schools in Mother and Child Health clinics at public hospitals, which are provided in all provinces and districts in Thailand as 'standard care'.

The study will also assess the process of implementation.

Inclusion criteria for programme facilitators, who will deliver ParentChat, consist of the following:

1. Age 18 or older;
2. Prior completion of a ParentChat facilitator training workshop;
3. Agreement to implement the entire programme; and
4. Provision of consent to participate in the full study.

Inclusion criteria for in-depth interviews with caregivers (n = 12):

1. 4 high engagement (participate  $\geq$  6 sessions)
2. 4 low engagement (participate  $\leq$  4 sessions)
3. 4 participants who drop out before 4th session
4. Provides consent to participate in the interview

Inclusion criteria for focus groups with facilitators:

1. Age 18 or older;
2. Have delivered the entire ParentChat programme; and
3. Provision of consent to participate in the full study.

